## Abstract

**Introduction:**

Acupuncture is an effective and safe therapy for patients with migraine without aura (MwoA), but only 41–59% of patients show improvement with this treatment. Screening positive responders to acupuncture treatment for MwoA can ensure that healthcare resources can be appropriately targeted to specific patients who would most benefit. The objective of this study is to determine whether the structure and functional activity in certain brain regions can predict analgesia response in patients with MwoA who receive acupuncture treatment.

**Methods and analysis:**

A total of 72 patients with MwoA and 72 healthy controls (HCs) will be enrolled in this study. Resting-state structural and functional magnetic resonance imaging (MRI) data will be collected from each participant at baseline. Patients with MwoA will undergo 12 sessions of acupuncture treatment for 8 weeks, twice per week in the first 4 weeks and once per week for the last 4 weeks. The follow-up will be 12 weeks. The number of days with migraine, frequency of migraine attacks, and average visual analog scale scores will be recorded in detail at weeks 0, 4, 8, 12, and 16 and at the end of follow-up (week 20). The positive response rate will be calculated as the proportion of patients with ≥50% reduction in the number of migraine days during follow-up compared with baseline. Machine learning methods will be applied to classify patients with MwoA and HCs and predict patients with response or non-response to acupuncture treatment based on multimodal MRI parameters, such as gray matter volume, regional homogeneity, amplitude of low-frequency fluctuation, fractional anisotropy, and mean diffusivity.

**Discussion:**

This study aims to establish brain structural and functional characteristics that can identify patients with MwoA who will derive analgesia benefits from acupuncture treatment.

**Trial registration number:**

http://www.chictr.org.cn/showproj.aspx?proj=65443, identifier: ChiCTR2100042915.

## Introduction

Migraine is a common neurologic disorder characterized by recurrent attacks of disabling headaches that are often accompanied by nausea, vomiting, photophobia, and phonophobia (1). Migraine is the 7th leading cause of time spent disabled worldwide (2), with an estimated 1-year prevalence of 15% in the general population (3). At present, there are no satisfactory treatments for migraine (4–6). Acupuncture, an important component of traditional Chinese medicine, is recommended by the World Health Organization as an alternative and complementary therapy for migraine. Many randomized controlled trials and systematic reviews have demonstrated that acupuncture is safe and cost-effective with comparable efficacy to prophylactic drugs for migraine and can reduce headache intensity, frequency of migraine attacks, and number of migraine days (7–10).

However, only 41–59% of patients with migraine without aura (MwoA) experience symptom improvement with acupuncture treatment (9). This is associated not only with clinical but also with socioeconomic challenges. Therefore, identifying characteristics that can be used to predict migraineurs' response to acupuncture is important to improve the efficacy of the treatment and provide individualized therapy to patients who would most benefit.

Personalized medicine can be achieved by conducting clinical trials, assessing clinical outcomes, analyzing numerous characteristics, and identifying common and unique predictors of treatment outcomes. Previous studies have reported that patients' expectations, educational background, and treatment preferences influence the clinical efficacy of acupuncture for diseases characterized by pain (11–15). However, the questionnaires used in these studies were subjective and qualitative. Recently, with the development of neuroimaging techniques and artificial intelligence, magnetic resonance imaging (MRI) data have been used to predict the clinical efficacy of various interventions, including pharmacologic treatments (16), cognitive behavioral therapy (17), and placebo treatments (18), among others. These studies often provide more objective and reliable predictions than questionnaires.

Patients with MwoA show widespread structural and functional changes in cortical and subcortical brain regions (19, 20). Acupuncture can potentially alleviate brain dysfunction in migraineurs in a specific way (21–24). Some studies have used either structural or functional parameters of different brain regions to predict the efficacy of verum or sham acupuncture treatment for chronic pain diseases (18, 25–27), demonstrating that objective neuroimaging parameters can be used to predict the analgesic efficacy of acupuncture treatment in patients with migraine.

The aim of this study is to identify brain features detected by multimodal MRI that can be used to predict the response to acupuncture treatment. To this end, multimodal MRI indicators from patients with MwoA and healthy controls (HCs) will be analyzed, then an advanced multivariate pattern analysis (MVPA) based on support vector classification (SVC) will be conducted through training, validation, and testing approach to classify migraineurs and HCs. Responders and non-responders of acupuncture treatment for patients with MwoA will be identified by the clinical outcomes obtained before vs. after treatment. The efficacy of acupuncture will be predicted by support vector regression (SVR) based on multimodal MRI data detected at baseline.

## Methods and analysis

### Study design

This non-randomized clinical trial will enroll 72 patients with MwoA and 72 with HCs. The study will last 24 weeks including a 4-week baseline period; for migraineurs, this will be followed by an 8-week treatment period and a 12-week follow-up period (Table 1). Structural and functional MRI scans will be performed at baseline. Clinical outcomes will be evaluated after treatment and during the follow-up. Figure 1 shows a flow diagram of the study. This protocol is reported in accordance with Consolidated Standards of Reporting Trials and Standards for Reporting Interventions in Clinical Trials of Acupuncture. The protocol was approved by the Institutional Review Board and Ethics Committee of the Hospital of Chengdu University of Traditional Chinese Medicine (approval no. 2020KL-058) and is registered with the Chinese Clinical Trial Registry (registration no. ChiCTR2100042915).

**Table 1 T1:** Standard protocol items: recommendations for interventional trials (SPIRIT) schedule of the trial.

**Study period**							
**Items**	**Screening**	**Baseline**	**Treatment**		**Follow-up**		
**Timepoint**	**week 4**	**week 0**	**week 4**	**week 8**	**week 12**	**week 16**	**week 20**
**Enrolment**	
Eligibility screen	**×**						
Informed consent	**×**						
**Intervention**	
Acupuncture					
**Assessments**	
Headache diary							
Number of days with headache	**×**	**×**	**×**	**×**	**×**	**×**	**×**
Frequency of headache attacks	**×**	**×**		**×**			**×**
Average VAS score	**×**	**×**	**×**	**×**	**×**	**×**	**×**
SAS score		**×**	**×**	**×**	**×**	**×**	**×**
SDS score		**×**	**×**	**×**	**×**	**×**	**×**
Use of NSAIDs	**×**	**×**		**×**			**×**
**Participants safety**	
Laboratory test		**×**		**×**			
MRI scan		**×**					
Adverse events							

This is a clinical trial that includes a 4-week baseline period, 8-week treatment period, and 12-week follow-up period. In the baseline period, eligible patients with MwoA will be screened and recruited. Before the treatment, patients will undergo a physical examination and structural and functional MRI scans. During the 8-week treatment period, patients will undergo 12 acupuncture sessions. The clinical outcome assessment will include the number of days with headache, frequency of migraine attacks, average VAS score, SAS score, SDS score, and use of non-steroidal anti-inflammatory drugs. In addition, patients will keep a headache diary in which they will record each migraine attack experienced during the trial. The physical examination, which will include routine blood biochemistry, will also be performed at the end of the treatment period to evaluate the potential risks associated with acupuncture. Adverse events occurring at any time during the trial will be recorded.

a. VAS, Visual Analog Scale; SAS, Self-rating Anxiety Scale; SDS, Self-rating Depression Scale; NSAIDs, Non-steroidal Anti-inflammatory Drugs. Laboratory test: including routine examination of blood, urine and stool, blood biochemical test (including liver and kidney function), and electrocardiogram examination.

**Figure 1 F1:**
[figure not shown]
Study flowchart. The flowchart of this study.

### Participants

Seventy-two patients with MwoA and 72 with HCs will be recruited for this study. Inclusion criteria for patients with MwoA are as follows: (1) aged 18–60 years; (2) right handed; (3) diagnosed with MwoA according to the 2018 International Classification of Headache Disorders (ICHD-3) (1); (4) have a history of migraine for over 6 months; (5) have had migraine attacks 3–15 times per month in the past 3 months; (6) did not take prophylactic headache medicine or receiving acupuncture treatment in the previous 3 months; and (7) signed the informed consent form.

Exclusion criteria were as follows: (1) suffering from psychiatric, neurologic, cardiovascular, respiratory, or renal illness; (2) suffering from any other chronic pain conditions or have a history of head trauma with loss of consciousness; (3) alcohol or drug abusers; (4) are pregnant or lactating; (5) have acupuncture contraindications such as bleeding tendency; and (6) have MRI contraindications such as claustrophobia.

Inclusion criteria for HCs are as follows: (1) aged 18–60 years; (2) right handed; and (3) free of any diseases. HCs will be excluded if they meet the following criteria: (1) have drug or alcohol addiction; (2) have contraindications for MRI; and (3) pregnant or lactating.

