#### Classification and prediction using machine learning methods

Multivariate pattern analysis (34) will be carried out to classify migraineurs and HCs; this will include feature selection, model construction, and performance evaluation. Principal component analysis (35) will be performed and the searchlight algorithm (36) will be used to select features from multimodal parameters of brain regions, such as gray matter volume (GMV), ReHo, ALFF, fALFF, FA, and MD. The linear kernel support vector classification will be used to construct the classification model (37), which will be assessed by leave-one-out cross-validation (LOOCV). Clusters with a minimum accuracy of 70% will be identified as meaningful classifying features.

Patients with MwoA will be divided into the response and non-response groups (defined as ≥50% and <50% reduction, respectively, in the number of migraine days end of treatment compared with baseline). Support vector regression will be performed to discriminate between the response and non-response groups using the abovementioned classifying features of brain regions (ie, GMV, ReHo, ALFF, fALFF, FC, FA, and MD) (38). In addition to neuroimaging features, we may combine multidimensional features such as clinical data to build the model. After constructing the prediction model for patients with MwoA, LOOCV will be performed to evaluate the robustness of the model. A receiver operating characteristic (ROC) curve will be generated, and the area under the curve (AUC, 0–1) will be calculated to assess the power of the model. The performance of the SVR model will be quantified by calculating sensitivity and specificity based on the number of true positives and true negatives.

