### Quality control

Diagnostic, inclusion and exclusion criteria will be strictly applied to screen participants. Patients with MwoA and HCs will be matched in age and education, and patients with average headache VAS scores at baseline >3 will be included. Before the study, the acupuncturists will undergo standardized training and will be required to strictly control the manipulation of the acupuncture needle to minimize interindividual differences. MRI data collection will be carried out according to the operating procedures and experimental design. Communication with patients will be controlled to minimize the influence of the environment and other factors.

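### Controls and patients enter under different general-health rules, so the patient-versus-control classifier can partly reflect health rather than migraine (minor; cheap to check)

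*Protocol article*

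**What the plan says.** The eligibility criteria for both groups stand in the Participants section of the protocol article. A control must be "right handed; and (3) free of any diseases"; the control exclusions then add substance addiction, MRI contraindications, and pregnancy or lactation ("HCs will be excluded if they meet the following criteria: (1) have drug or alcohol addiction; (2) have contraindications for MRI", with pregnancy as the third item).

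Patients have no general requirement of health. They are excluded for "suffering from psychiatric, neurologic, cardiovascular, respiratory, or renal illness", for "suffering from any other chronic pain conditions or have a history of head trauma with loss of consciousness", as "alcohol or drug abusers", for pregnancy or lactation, for acupuncture contraindications such as a bleeding tendency, and for MRI contraindications. The only medicine restricted by the eligibility criteria is prophylactic headache medicine in the previous 3 months.

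Under Quality control the only matching is this: "Patients with MwoA and HCs will be matched in age and education". Planned sizes are equal: "Seventy-two patients with MwoA and 72 with HCs will be recruited for this study".

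The section on classification and prediction trains a linear support vector classifier on patients versus controls and keeps clusters with at least 70% accuracy. It then builds the response model "using the abovementioned classifying features of brain regions".

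**The concern.** In a case-control classification, anything that eligibility builds into one group and removes from the other is available to the classifier. Here a patient with, say, diabetes or thyroid disease is eligible and a control with either is not. If such a disease or its treatment alters grey matter volume, diffusion measures or resting-state activity, some of the separation between the groups is health status, yet it would be reported as a feature of migraine. Leave-one-out cross-validation does not expose this, because the imbalance is present in every fold.

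At stake is, first, the reading of the patient-versus-control result, which is a stated aim. Second is the choice of features, because the clusters kept at this step are those offered to the response model.

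**Working it through.** **1. The two rules side by side**

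| Condition | Patients | Controls |
|---|---|---|
| Psychiatric, neurologic (migraine aside), cardiovascular, respiratory, renal illness | excluded | excluded (any disease) |
| Other chronic pain | excluded | excluded (any disease) |
| Alcohol or drug abuse/addiction; pregnancy or lactation; MRI contraindication | excluded | excluded |
| Endocrine/metabolic, hepatic, gastrointestinal, autoimmune disease | not named | excluded (any disease) |
| Past head trauma with loss of consciousness | excluded | not named |

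The rules differ in the last two rows, in opposite directions. Neither is addressed by matching on age and education.

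**2. Could the allowed disease reach the 70% mark alone?**

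The article states no figure to reproduce, so this is a size check. Inputs from the article: 72 patients, 72 controls, 70% mark. Assumed, because the article does not give them: p, the share of patients with an allowed disease (0 in controls), and s, the extent to which a cluster reveals that disease.

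With equal groups, expected accuracy from health status alone = 0.5 + p·s/2.

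| p | s = 0.5 | s = 1 |
|---|---|---|
| 5% | 51.25% | 52.5% |
| 10% | 52.5% | 55% |
| 20% | 55% | 60% |
| 40% | 60% | 70% |

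Setting 0.5 + p/2 = 0.70 gives p = 40%, that is 0.4 × 72 = 28.8, or about 29 patients.

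The chance of passing: 70% of 144 is 100.8, so 101 correct are needed. A perfect marker (s = 1) gets all 72 controls right and so needs 101 − 72 = 29 patients right. With X ~ Binomial(72, p), P(X ≥ 29) is below 0.001 at p = 20%, 0.04 at 30% and 0.53 at 40%.

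**3. Could it tip a borderline cluster?**

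Take a cluster whose true migraine accuracy is 65%, with sensitivity = specificity = 0.65, and treat classifications as independent. If it also reveals the allowed disease, sensitivity becomes 0.65 + p·s·(1 − 0.65) and specificity stays at 0.65. The probability of at least 101 correct out of 144 is the upper tail of the sum of two binomials of size 72.

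| p | s | Sensitivity | P(cluster retained) |
|---|---|---|---|
| 0 | – | 0.650 | 0.11 |
| 10% | 0.5 | 0.6675 | 0.16 |
| 10% | 1 | 0.685 | 0.22 |
| 20% | 0.5 | 0.685 | 0.22 |
| 20% | 1 | 0.720 | 0.37 |

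Under full detectability, retention roughly doubles at p = 10% and triples at p = 20%. The s = 1 rows are ceilings, since one cluster would have to mark a mixed set of diseases without error.

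**4. What reaches the response model?**

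Responders and non-responders are all patients, admitted under one set of criteria, and controls do not enter that comparison. A cluster retained partly because of general health is therefore a poorly chosen input. The control rule by itself gives it no association with response.

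**The case against.** The strongest reply is that the patient exclusions are not thin. They already remove psychiatric, neurologic and cardiovascular illness, other chronic pain, head trauma and substance abuse, the conditions most directly tied to brain structure and function. What remains is a residual group of diseases in people aged 18 to 60. Requiring healthy controls to be free of disease is a coherent choice, and the article contains no wrong figure here. This stands, and it is why the point is minor.

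It can also be said that p and s are assumed and that 60% accuracy from health alone needs both p = 20% and perfect detection. That stands too. The figures show a range and are not an estimate of the bias.

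A third reply is that the full protocol may handle comorbidity, and that the Patient safety section plans blood, urine, stool, biochemistry and ECG tests for each participant before enrolment. This holds only in part. How test results are used and which covariates enter the image analysis may properly be left to documents not shown. The unequal criteria, however, are not an omission: the article lists both sets, and they differ.

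Two stronger readings should be resisted. A reader might infer that general health alone could produce the classifying clusters; step 2 of the working shows that this needs about 40% of patients to be affected. A reader might also infer that the control rule biases the prediction of response. The documents do not support that, because the response model compares patients with patients.

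**Conclusion.** The point holds as a minor design weakness. The two groups are admitted under different non-migraine health rules, the rules differ in both directions, and the stated matching offsets neither. The patient-versus-control classifier can partly reflect general health.

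The allowed disease is unlikely to meet the 70% mark alone, but it can raise the chance that a borderline cluster is kept: in the 65% example, from 0.11 to between 0.16 and 0.37 over the assumed range (p of 10% to 20%, s of 0.5 to 1). That example rests on independent classifications and on a cluster that marks both migraine and the other disease. For the response model the consequence is less useful inputs, not a false signal.

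**What to change.** 1. Record other current diagnoses and regular medicines in both groups, including participants already enrolled.
2. Apply the exclusion for head trauma with loss of consciousness to controls as well.
3. Repeat the classification, with its feature selection, leaving out participants who have a non-migraine disease or take a regular medicine for one. Report whether the retained clusters change. Mostly patients will drop out, so report balanced accuracy or restore equal groups. With 7 patients removed (about 10%), for example, calling everyone a control would already score 72/137 = 52.6%.
4. Where recruitment still allows (15 patients had been recruited when the article was written), apply one common non-migraine health criterion to both groups. Whether to tighten the patient rule or loosen the control rule is open to debate: the first loses some eligible patients, the second makes controls less uniform.

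The cost of items 1 to 3 is two fields on the case report form, one line of eligibility wording, and one repeat analysis on a slightly smaller sample. Because clusters near 70% can drop out by chance in a smaller sample, give the accuracies from both analyses and not only pass or fail.

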### Participant recruitment

All MwoA patients and HCs will be recruited as outpatients and inpatients of the Neurology Department of the Hospital of Chengdu University of Traditional Chinese Medicine or from the community through advertising from March 2021 to December 2023.

### Blinding

This trial follows the principle of separation of researchers, evaluators, and statistical analysts.

### Interventions

HCs will not receive any treatment during the trial. All patients with MwoA will receive the same acupuncture treatment procedure. *Baihui* (GV20), bilateral *Fengchi* (GB20), bilateral *Touwei* (ST8), bilateral *Shuaigu* (GB8), bilateral *Taiyang* (EX-HN5), bilateral *Hegu* (LI4), and bilateral *Taichong* (LR3) will be targeted by the acupuncture treatment (Figure 2).

**Figure 2 F2:**
[figure not shown]
Location of Acupoints. DU20 (*Baihui*): on the head, five *cun* directly above the midpoint of the anterior hairline or at the midpoint of the line connecting the apexes of the two auricles. GB20 (*Fengchi*): on the nape, below the occiput in the depression between the upper portion of the trapezius and sternocleidomastoid. ST8 (*Touwei*): at the lateral side of the head, within 0.5 *cun* of the hairline at the corner of the forehead, and 4.5 *cun* lateral to the median line of the head. GB8 (*Shuaigu*): on the head above the apex of the auricle and SJ-20 (*Jiaosun*), within 1.5 *cun* of the hairline. EX-HN5 (*Taiyang*): in the region of the temples, in the depression about one finger-width posterior to the midpoint between the lateral end of the eyebrow and outer canthus. LI4 (*Hegu*): on the dorsum of the hand, between the 1st and 2nd metacarpal bones, at the midpoint of the 2nd metacarpal bone on the radial side. LR3 (*Taichong*): on the dorsum of the foot, in the depression proximal to the first metatarsal space.

The acupuncture procedure is as follows: after skin disinfection, needles (diameter, 0.25 mm and length, 15 or 40 mm; Hwatuo, Suzhou, China) will be inserted vertically or horizontally into each point. After eliciting *deqi* (28), the needles will be kept in place for 60 min with manipulation twice for 10–15 s every 20 min.

Patients will undergo 12 sessions of acupuncture treatment for a total of 8 weeks, twice per week in the first 4 weeks and once per week for the last 4 weeks. All acupuncture manipulations will be performed by two trained and licensed acupuncturists.

### Medications

In cases of severe pain for migraineurs, ibuprofen will be allowed as rescue medication. The use of medication will be recorded in detail during the trial.

### Outcome assessment

#### Clinical outcomes

Data acquisition will be performed by independent assessors who have received professional training before the start of the study. Clinical outcomes are as follows:

